## Abstract

**Introduction::**

Upper extremity motor impairment is one of the major sequelae of stroke, resulting in limitations of activities of daily living. Recently, contralesional cortical activation has been reported to be important for motor recovery in stroke patients with severe upper extremity hemiparesis due to the extensive corticospinal tract involvement. We therefore designed this study to investigate the effects of contralesional anodal transcranial direct current stimulation (tDCS), which induces cortical activation, in stroke patients with severe upper extremity motor impairment.

**Methods and analysis::**

We will recruit patients with subacute stroke (<3 months after onset) with unilateral upper extremity weakness who meet the following criteria: Shoulder Abduction and Finger Extension (SAFE) score below 8, Fugl-Meyer Assessment for upper extremity (FMA-UE) score ≤25, and absent motor evoked potential (MEP) response on the affected extensor carpi radialis muscle. Subjects will be randomly allocated to either the intervention (n = 18) or the control group (n = 18). The intervention group will undergo 10 sessions of robotic arm rehabilitation with simultaneous anodal tDCS over the contralesional premotor area, whereas the control group will receive sham tDCS during the same sessions. One daily session consists of 25 minutes.

The primary outcome measure of this study is the Fugl-Meyer Assessment score of the upper extremity; the secondary outcome measures are the Korean version of the Modified Barthel Index, the Brunnstrom stage of the affected arm and hand, the Box and Block Test, the Modified Ashworth Scale, the Manual Muscle Power Test, and the patient's encephalographic laterality index.

**Discussion::**

Findings of this study will help to establish an individualized tDCS protocol according to the stroke severity and to find out the EEG parameters to predict the better recovery in subacute stroke patients with severe upper extremity hemiparesis.

**Ethics and Dissemination::**

The study was approved by the Seoul National University Bundang Hospital Institutional Review Board (IRB No. B-1806-475-006) and will be carried out in accordance with the approved guidelines. The results of the trial will be submitted for publication in a peer-reviewed journal.

## Introduction

1

Upper extremity motor impairment is one of the major sequelae of stroke, resulting in limitations of activities of daily living (ADL) and lowered quality of life.^[1,2]^ After stroke, damage to the ipsilesional primary motor cortex (M1) results in an imbalance between the 2 hemispheres (hypoexcitability of ipsilesional M1 and hyperexcitability of contralesional M1), with greater imbalance associated with worse outcomes.^[3]^ Transcranial direct current stimulation (tDCS) has therefore traditionally been used to reduce the imbalance between the two hemispheres, based on the “interhemispheric inhibition (IHI) model.”^[4–6]^ Anodal tDCS over ipsilesional M1 is used to directly increase excitability in ipsilesional M1, whereas cathodal tDCS over contralesional M1 is used to suppress the overexcitability of contralesional M1 and abnormally high IHI from contralesional to ipsilesional M1, which results in an increase in ipsilesional M1 excitability.^[7,8]^

However, contralesional cathodal tDCS and repetitive transcranial magnetic stimulation have yielded conflicting results on upper limb functional recovery after stroke,^[9–12]^ which might be associated with the diversity of participants’ severity of upper limb hemiparesis and chronicity after stroke. For example, patients with stroke with severe damage to the ipsilesional corticospinal tract showed poor responses to cathodal tDCS of contralesional M1, whereas patients with less damage showed good responses.^[13]^ Di Pino et al therefore suggested the “bimodal balance-recovery model,”^[5,14]^ in which the role of the activation of the contralesional hemisphere in recovery depends on the degree of corticospinal tract damage. This model postulates that IHI is less important for recovery in severe upper extremity hemiparesis, and that contralesional cortical activation induced by anodal tDCS over the contralesional hemisphere may contribute to functional recovery; this hypothesis has however not been tested in patients in a clinical trial. In addition, IHI has only been demonstrated in patients with chronic stroke.^[15,16]^ Recently, a longitudinal study in patients with stroke using paired transcranial magnetic stimulation demonstrated that an IHI imbalance in subacute stroke is not associated with worse motor recovery, which calls into question the use of cathodal tDCS over contralesional M1 in acute or subacute stroke.

Therefore, this study primarily aims to investigate the effects of anodal tDCS over the contralesional premotor cortex on motor recovery in patients with subacute stroke with severe upper extremity hemiparesis who can expect no meaningful recovery in a conventional rehabilitation setting, according to the PREP algorithm suggested by Stinear et al.^[17]^ Robotic arm rehabilitation therapy was selected as a concurrent rehabilitation modality due to its possible beneficial effects on motor recovery in severely impaired patients with stroke.^[18,19]^ Secondarily, the neurophysiological changes induced by tDCS will be investigated using electroencephalography (EEG), and used to further investigate neurophysiological substrates and markers which differentiate responders from nonresponders for this new tDCS approach.

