### Assessment

2.7

Assessments will be conducted 3 times: at baseline (T0), after 2 weeks of intervention (T1), and at 4 weeks post-intervention (6 weeks post-baseline) (T2). The T0 assessment is conducted within 7 days before the start of the therapy session, the T1 assessment within 3 days after the end of the therapy session, and the T2 assessment within 7 days from day 30 after the start of the therapy session. At the T0 assessment, additional information on the participants’ baseline characteristics, including sex, age, stroke type, side of brain lesion, lesion area, stroke duration, and the initial National Institutes of Health Stroke Scale (NIHSS) score, will be collected. The NIHSS score measures neurologic deficits according to 11 categories, and the score ranges from 0 to 42, with 0 indicating no abnormality. Excellent specificity, sensitivity, and accuracy in predicting outcomes have been reported.^[22,23]^ As for the outcome measures, the primary outcome measure FMA-UE and all secondary outcome measures except the EEG laterality index (LI) (modified Rankin Scale [mRS], Korean version of the Modified Barthel Index [K-MBI], Brunnstrom stage of the arm and hand, the Box and Block Test [BBT], the Modified Ashworth Scale [MAS] of the wrist flexor/extensor, elbow flexor/extensor, and finger flexor, and the Medical Research Council [MRC] Scale of shoulder abduction, elbow flexion/extension, wrist flexion/extension, and finger flexion/extension) will be assessed 3 times. The EEG LI will be assessed twice, at T0 and at T1. Assessments last approximately 1.5 hours and regular breaks will be scheduled to mitigate fatigue and burden.

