#### Secondary outcomes

2.8.2

Secondary outcomes are the change in FMA-UE scores between T0 and T2, and the changes in mRS scores, K-MBI scores, Brunnstrom stages, BBT scores, MAS scores of the wrist flexor/extensor, elbow flexor/extensor, and finger flexor, MRC Scale scores of shoulder abduction, elbow flexion/extension, wrist flexion/extension, and finger flexion/extension between T0 and T1 and between T0 and T2, as well as the change in the EEG LI between T0 and T1.

The mRS is a categorical measure of disability incorporating mental and physical status after neurological deficits. The scale consists of 6 grades, from 0 (no symptom at all) to 5 (severe disability), and 6 (death).^[25]^ The K-MBI is the Korean version of the MBI, which measures the degree of independence of ADL according to 10 items, with the total score ranging from 0 (completely dependent) to 100 (independent).^[26]^ The Brunnstrom stage is the motor recovery stages after stroke, with the recovery process classified into six stages from 1 (flaccidity with no movements of the limbs) to 6 (individual joint movements).^[27]^ The BBT is a measure of gross manual dexterity, assessed by counting the number of blocks moved from one compartment to another across the partition in 60 seconds, with proven validity.^[28]^ The MRC is an ordinal scale of muscle power, with proven reliability, and the MAS is a scale of spasticity which is graded from 0 to 4, larger numbers indicating more increased resistance to passive movement of the joints.^[29,30]^

The EEG LI will be calculated to measure the lateralization of cortical activity during rest and task performance. LI is calculated as LI = (NL-NR)/(NL+NR), and values range between −1 and 1. An LI > 0.2 indicates a predominance of right cerebral cortical activity, an LI < −0.2 indicates predominance of left cerebral cortical activity, and an LI between −0.2 and 0.2 is considered “not lateralized.”^[31]^

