### Statistical analysis

2.12

The primary analysis will be done on a modified intention-to-treat (ITT) population of participants who were randomly assigned to groups and underwent >1 therapy session. Participants who complete the 10 tDCS sessions and all 3 (T0, T1, and T2) assessments per protocol will be included for the secondary endpoint analysis to verify a sustained clinical response. For between-group comparisons of baseline characteristics, Student *t* tests or Mann–Whitney *U* tests for continuous variables and *χ*^2^ tests or Fisher exact test for categorical variables, depending on normality, will be used. Student *t* tests or Mann–Whitney *U* tests will be performed to investigate if the changes in primary and secondary outcome measures are different between the anodal tDCS and sham group. All statistical analyses will be performed using SPSS (version 25.0), and *P* values <.05 will be considered statistically significant. In the repeated measures analysis including assessments of T2, Bonferroni correction will be applied and the significance level will thus be adjusted to 0.05/2 = 0.025.

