## Discussion

3

This study aims primarily to investigate the effects of anodal tDCS over the contralesional premotor cortex in patients with subacute stroke with severe upper extremity hemiparesis. Under the concept of IHI model, contralesional cathodal tDCS has been used with conflicting results. Therefore, another model called “bimodal balance-recovery model” is introduced highlighting ∼ the promotion of contralesional cortex function in stroke with severe motor impairment. This will be the first randomized controlled trial investigating the effect of contralesional anodal tDCS in patients with subacute stroke with severe upper extremity motor impairments. The expected results will be better outcome measure improvements in anodal tDCS group than sham tDCS group. Secondarily, the EEG signals are collected to further investigate neurophysiological markers to predict responders or nonresponders for this new tDCS protocol. Results of this study will help to establish a new EEG signal-based precise tDCS protocols for stroke patients with severe motor impairment.

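### The stated EEG endpoint and test show whether tDCS shifts laterality; they do not address the secondary aim of finding markers of who responds to tDCS

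*Protocol article*

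**What the plan says.** **Aim.** The Introduction (section 1) says that the changes seen on EEG under tDCS will be "used to further investigate neurophysiological substrates and markers which differentiate responders from nonresponders for this new tDCS approach". The Discussion (section 3) puts this as prediction: "the EEG signals are collected to further investigate neurophysiological markers to predict responders or nonresponders for this new tDCS protocol". The abstract's Discussion hopes "to find out the EEG parameters to predict the better recovery in subacute stroke patients with severe upper extremity hemiparesis". Section 3 adds: "Results of this study will help to establish a new EEG signal-based precise tDCS protocols for stroke patients with severe motor impairment".

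**Endpoint.** Section 2.8.2 ends its list of secondary outcomes with "as well as the change in the EEG LI between T0 and T1". Section 2.7 gives the timing: "The EEG LI will be assessed twice, at T0 and at T1".

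**Analysis.** Section 2.12 provides Student t tests or Mann-Whitney U tests to "investigate if the changes in primary and secondary outcome measures are different between the anodal tDCS and sham group". It states no other analysis for the EEG data.

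**The concern.** The aim and the analysis ask different questions. A between-arm test of LI change asks whether stimulation moves LI on average. A marker of response asks in which patients stimulation improves motor outcome more than sham does. The first does not answer the second.

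Two features of the stated plan add to the mismatch. The LI change is complete only at T1, the visit that also completes the primary outcome, so it cannot be known before treatment. And the responder/non-responder wording invites sorting patients by their own FMA-UE gain, which counts any gain that would have happened under sham as a response to tDCS.

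At stake is a named secondary aim and the claim in section 3 about EEG-based tDCS protocols. The primary analysis is not affected.

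**Working it through.** **1. Questions side by side**

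| Question | Data needed | Stated in the protocol? |
|---|---|---|
| Does tDCS shift LI? | LI change by arm | Yes (2.8.2, 2.12) |
| Does EEG predict recovery in general (abstract)? | T0 EEG against FMA-UE change | Data collected, no analysis stated |
| Does EEG predict benefit from tDCS (sections 1 and 3)? | T0 EEG, arm and their interaction on FMA-UE change | Data collected, no analysis stated |

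**2. The plan's own sample size**

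Inputs from section 2.10: difference 10 (upper end of 9 to 10), SD 10, two-sided 5%, power 80%, drop-out 10%.

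- n per arm = 2 × (1.960 + 0.842)² × (10/10)² = 15.7, so 16.
- 16 / 0.9 = 17.8, so 18 per arm and 36 in total. The stated figure is reproduced.

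I carry forward 16 evaluable per arm and read the SD of 10 as the within-arm SD of FMA-UE change.

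**3. Precision of an analysis that fits the aim**

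- Continuous T0 marker, slope difference per 1 SD of the marker: SE = 10 × √(2/16) = 3.54. Detectable with 80% power: 2.802 × 3.54 = 9.9 points. Half-width of the 95% CI: 1.96 × 3.54 = 6.9 points.
- Marker split at the median, 8 per cell: SE = 10 × √(4/8) = 7.07. Detectable: 2.802 × 7.07 = 19.8 points (20.5 with the t distribution). Half-width: 1.96 × 7.07 = 13.9 points. Power for a 10-point interaction: Φ(10/7.07 − 1.96) = Φ(−0.55) = 29%.
- With all 18 per arm the detectable values are 9.3 and 18.7 points, so full retention changes little.

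**4. What a label based on a patient's own gain would capture**

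Assumptions, since the protocol gives no sham gain and no responder definition: responder means a gain of at least 9 points, SD 10, tDCS adds 10 points to every patient, and the mean sham gain is 0, 5 or 10. The sham share is 1 − Φ((9 − m)/10) and the anodal share is 1 − Φ((9 − m − 10)/10).

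| Mean sham gain m | Sham responders | Anodal responders | Ratio |
|---|---|---|---|
| 0 | 18.4% | 54.0% | 0.341 |
| 5 | 34.5% | 72.6% | 0.475 |
| 10 | 54.0% | 86.4% | 0.625 |

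The ratio is the share of anodal responders who would have passed the threshold without stimulation. Even with no mean sham gain it is about a third.

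**The case against.** **The article is condensed.** A responder definition and an exploratory model may stand in the full protocol or an analysis plan, neither of which is shown. This stands: their absence alone is not the point. What remains is that the article fixes an EEG endpoint and a test, and these do not fit the aim that it states.

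**The aim is partly mechanistic.** The Introduction also speaks of substrates, and the between-arm test of LI change serves that part well. The abstract's wording is prognostic and needs no interaction. Both are fair. Predicting responders to this tDCS protocol, as section 3 puts it, is still not addressed.

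**Little recovery is expected.** The Introduction selects patients for whom conventional rehabilitation promises no meaningful recovery. But both arms also receive ten robot sessions, chosen for a possible motor benefit, within three months of onset. Some sham gain is plausible and its size is unknown.

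Three stronger readings are tempting but not supported:

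- *The aim cannot be met.* LI is measured at T0, FMA-UE at T0 and T1, in a randomized two-arm design. The data for a suitable analysis will exist.
- *The trial cannot tell a tDCS effect from spontaneous recovery.* The sham arm does this at group level. The difficulty concerns individual labels and analyses confined to the active arm.
- *The plan will often report a purely prognostic marker as predictive.* A test within the active arm alone would be significant in about 20% of trials at a correlation of 0.3 and 54% at 0.5, against 5% for the interaction test. Those correlations are assumed, and the protocol nowhere proposes such a test. The figures support using both arms; they are not evidence about this plan.

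**Conclusion.** The point holds as a mismatch between aim and analysis. Section 2.12, as written, can show whether tDCS shifts LI; it cannot show which patients benefit from tDCS. The design allows an analysis that fits the aim, but with 32 evaluable patients it is imprecise: about 10 FMA-UE points per SD of a continuous marker, or about 20 for a median split, for 80% power. The smaller of these is as large as the whole effect for which the trial is powered. The marker results can therefore only generate hypotheses, and the statement about EEG-based protocols in section 3 goes further than the trial can support.

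The precision figures rest on the protocol's SD and drop-out rate, on reading that SD as the SD of change, and on the normal approximation. The responder shares rest on assumed sham gains, an assumed threshold and a constant effect, and serve only as illustration.

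**What to change.** In section 2.12:

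- Keep the T0-T1 change in LI, compared between arms, as a mechanistic outcome.
- For the marker aim, fit one exploratory linear model in both arms: T0-T1 FMA-UE change on arm, continuous T0 LI and their product. Report the interaction with its 95% CI.
- Re-sign LI as ipsilesional versus contralesional, using the lesion side recorded at T0. LI in section 2.8.2 is a left-versus-right contrast, so the raw value gives opposite signs to the same pattern in left- and right-sided lesions.
- Name in advance which LI enters the model, since section 2.8.2 computes it both at rest and during the task.
- Do not define responders by improvement within the active arm.

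Alternatively, narrow the secondary aim to the effect of tDCS on LI.

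In either case, describe the EEG marker results as exploratory and hypothesis-generating in the abstract's Discussion and in section 3.

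The cost is a few sentences and one model on data already being collected. The downside is a weaker stated claim and a wide interval, roughly ±7 points per SD of the marker.

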## Methods and analysis

2

### Study design

2.1

This study is a double-blind, randomized, sham-controlled trial conducted at a single center. The study was approved by the Seoul National University Bundang Hospital Institutional Review Board (B-1805/468-002), and written informed consent will be provided by all participants before enrolment. The study was registered at ClinicalTrials.gov (NCT03635008).

### Trial status

2.2

At the time of submission of this study protocol, subject recruitment is ongoing.

### No patient and public involvement

2.3

This research was done without patient involvement. Patients were not invited to comment on the study design and were not consulted to develop patient relevant outcomes or interpret the results. Patients were not invited to contribute to the writing or editing of this document for readability or accuracy.

### Participants

2.4

Inpatients at the rehabilitation medicine department at a single center will be screened for the study. The inclusion criteria include the following: age 18 to 85 years; first-ever stroke; ischemic or hemorrhagic stroke confirmed by magnetic resonance imaging or computed tomography; <3 months after stroke onset; and severe unilateral hemiplegic upper extremity impairment meeting the following conditions^[17]^: Shoulder Abduction and Finger Extension (SAFE) score <8, Fugl-Meyer Assessment for upper extremity (FMA-UE) ≤25, and absent motor evoked potential (MEP) response on the affected extensor carpi radialis muscle. The exclusion criteria were the following: history of brain disorders other than stroke that can cause motor deficits, such as traumatic brain injury or brain tumours; inability to follow instructions (indicated by a score ≤15 on the Korean version of the Mini-Mental State Exam^[20]^ or delirium or impaired consciousness); pregnancy; cardiac pacemakers, cochlear implants, or metals in the head (eg, clip, coil); scalp problems which might interfere with the tDCS application; poor sitting balance, poor head control, or severe upper extremity pain that could interfere with robotic arm rehabilitation; and uncontrolled severe medical conditions.

### Recruitment

2.5

Participants will be recruited from the inpatient rehabilitation department of Seoul National University Bundang Hospital. We will recruit 18 participants per group. The trial design is outlined in Figure 1. All potential participants will be screened for eligibility, and the principal investigator will provide them with information about the study. If patients are interested, the coinvestigators will provide additional information about the trial and obtain written informed consent from the participants. A list of the people screened and enrolled in the trial as well as reasons for ineligibility will be recorded. Recruitment commenced in July 2019.

**Figure 1 F1:**
[figure not shown]
Trial design. BBT = box and block test, EEG = electroencephalography, FMA-UE = Fugl-Meyer assessment for upper extremity, K-MBI = Korean version of the modified Barthel index, MAS = modified Ashworth scale, MRC = Medical Research Council, mRS = modified Rankin Scale, NIHSS = National Institutes of Health stroke scale, tDCS = transcranial direct current stimulation.

### Intervention

2.6

All participants will receive 25 minutes of robot-assisted therapy with the ArmeoPower device (Hocoma, Volketswil, Switzerland), daily on weekdays for 2 weeks, for a total of 10 sessions. The robot-assisted therapy will be managed by the same experienced occupational therapist who will choose the adequate program for each participant. According to the participant's group allocation, anodal tDCS or sham tDCS will be applied concurrently with the robot-assisted therapy. The experimental setup is demonstrated in Figure 2. The time used to adjust the tDCS setup and the robotic arm will not be counted as therapy time. All subjects will undergo an additional 30 minutes of conventional occupational therapy and will be permitted to engage in physical therapy to restore gait during the intervention period. Intervention will be halted at any time, on the participant's request or on the primary investigator's decision, upon any severe adverse events.

